### 10.1.2 Questionnaires for quality of life, depression and fatigue

Furthermore, the following self-administered questionnaire for evaluating the quality of life (QoL) will be used:

- EuroQuol-5D-DL [32]

(multiple choice questionnaire and a visual analogue scale) and takes only few minutes to complete. The EQ-5D-5L will be assessed at every visit.

The EQ-5D-5L is a standardized measure of health status and in order to provide a simple, generic measure of health for clinical and economic appraisal and consists of 2 parts - the *EQ-5D descriptive system* and the *EQ visual analogue scale (EQ VAS)*. The EQ-5D-5L descriptive system comprises the following 5 dimensions: mobility, self-care, usual activities, pain/discomfort and anxiety/depression.

Each dimension has 5 levels: no problems, slight problems, moderate problems, severe problems, and extreme problems.

As depression and fatigue are known common comorbidities in patients with cerebellar ataxia, two additional questionnaires will be used:

- Beck depression inventory (BDI-II) [24, 33, 34]

The Beck's Depression Inventory (BDI-II) is a multiple choice self-report inventory for measuring the severity of depression and is composed of items relating to symptoms of depression such as hopelessness and irritability, emotions such as guilt or feelings of being punished, as well as physical symptoms such as fatigue, weight loss and lack of interest in sex.

- Fatigue severity score (FSS) [34]

The Fatigue Severity Scale (FSS) captures the patient's experience of mental or psychological fatigue and how it interferes with performing certain activities (exercise, work and family life). It is a self-reporting scale using 9 items. The mean of all answered items represents the fatigue severity..

These questionnaires will be completed by the patients themselves. See also Appendix 22.3, 22.4 and 22.5.

### 10.1.3 Laboratory examinations / Biological Specimens

A routine blood-sample will be taken to exclude liver or kidney failure and a pregnancy test for women of childbearing potential. A pregnancy test is not required for postmenopausal (amenorrhea > 12 months), surgically sterilized or hysterectomized women. If a routine blood sample examination not older than 7 days prior to visit 1 is available, no renewed blood testing needs to be done. Blood sample examinations older than 7 days but not older than 30 days prior to visit 1 are considered a minor protocol violation.

The following parameters will be measured according to the time schedule given in section 2 (schedule of activities):

- Sodium
- Potassium
- Creatinine
- Serum bilirubin level
- AST
- ALT
- Urea
- ALP
- TSH
- Hemoglobin
- Erythrocytes
- Hematocrit
- Thrombocytes
- Leukocytes
- Pregnancy test for women of child bearing potential

The total amount of blood taken per subject during the entire trial will be approximately 20 ml. At each study center, the blood testing will be done by the in-house laboratory.

The results from the blood test will be reviewed and evaluated by one of the investigators of each study center in a timely manner. Clinically significant findings at screening visit 1 which describe the baseline status of the subjects will be documented as concomitant disease under medical history. In case of meeting any exclusion criteria, the patient cannot be included in the study.

## 10.2 Time schedule of Measurements

See Schedules of activities and assessments (section 2).

### 10.2.1 Screening period

Written informed consent will be obtained from all subjects before performing the first (study specific) screening procedure.

All subjects will be screened for inclusion and exclusion criteria before randomization. Only subjects meeting the inclusion and none of the exclusion criteria will be allocated to the trial.

#### Screening visit/ visit 1

- Check of inclusion/exclusion criteria
- Blood test including pregnancy test for women of child bearing potential
- Patient characteristics and medical history as well as medical history concerning the trial specific illness, including frequency of physiotherapy and speech therapy (documented in hours per week)
- Drug history including documentation of prior therapies/medications and concomitant medications for treatment of trial specific illness as well as drug history for other indications
- Documentation of concomitant medication
- Neurological examination
- Ataxia rating scale (SARA)

Patients on prohibited medication (i.e. medication for cerebellar ataxia like 4-Aminopyridine retarded, Acetyl-DL-Leucine etc.) at screening visit/ visit 1 have to wash-out these medications for 4 weeks and then continue with visit 2 (randomization and start of trial medication), resulting in a total study duration of 24 weeks.

### 10.2.2 Treatment period 1

The treatment period 1 will include 3 visits from week one until week 6.

A delay of -3 and +5 days is acceptable for visit 2, for all other visits a delay of  $\pm 5$  days is acceptable.

All visits will be performed according to the Schedule of Activities and Assessments (see Schedule of Activities and Assessments 2).

Visit 2

- Randomization
- Dispensing of trial drug
- Ataxia rating scales (SARA, SCAFI)
- Quality of life questionnaires (EQ-5D-5L, BDI-II, FSS)
- Documentation of adverse events
- Documentation of frequency of physiotherapy and speech therapy (hours per week)
- Documentation of concomitant medication

If patients aren't on any medication due to cerebellar ataxia, visit 2 and visit 1 can take place together. If visit 1 and visit 2 take place at the same date, ataxia rating scale (SARA) as well as documentation of adverse events and documentation of frequency of physiotherapy and speech therapy are assessed only once. Baseline level is defined as measurements taken at visit 2.

Visit 3 and visit 4

- Ataxia rating scales (SARA, SCAFI)
- Self-administered questionnaires (EQ-5D-5L, BDI-II, FSS)
- Documentation of adverse events
- Documentation of frequency of physiotherapy and speech therapy (hours per week)
- Documentation of concomitant medication
- Blood test including pregnancy test for women of child bearing potential (at visit 4 only)
- Return of trial drug at visit 4
- Compliance check

Visit 3 takes places after two weeks on medication, Visit 4 after six weeks on medication.

**10.2.3 Wash out**

A wash out period of 4 weeks will be performed between the two treatment periods (between visit 4 and 5)

#### 10.2.4 Treatment period 2

The treatment period 2 will start after a wash out period of 4 weeks (between visit 4 and visit 5) and will include 3 visits from week 10 to week 16.

A delay of -3 and +5 days is acceptable for visit 5, for all other visits a delay of  $\pm 5$  days is acceptable.

All visits will be performed according to the Schedule of Activities and Assessments (see 2).

##### Visit 5

- Dispensing of trial drug
- Ataxia rating scales (SARA, SCAFI)
- Self-administered questionnaires (EQ-5D-5L, BDI-II, FSS)
- Documentation of adverse events
- Documentation of frequency of physiotherapy and speech therapy (hours per week)
- Documentation of concomitant medication
- Blood test including pregnancy test for women of child bearing potential pregnancy test for women of child bearing potential

Visit 5 takes place after the wash-out period of 4 weeks.

##### Visit 6 and visit 7

- Ataxia rating scales (SARA, SCAFI)
- Self-administered questionnaires (EQ-5D-5L, BDI-II, FSS)
- Documentation of adverse events
- Documentation of frequency of physiotherapy and speech therapy (hours per week)
- Documentation of concomitant medication
- Blood test including pregnancy test for women of child bearing potential (only at visit 7)
- Documentation of concomitant medication
- Return of trial drug at visit 7
- Compliance check

Visit 6 takes place after two weeks on medication, visit 7 after 6 weeks on medication.

**Confidential**

### 10.2.5 Follow-up period

The follow-up period takes place after treatment period 2 and lasts for 4 weeks. The follow up ends with visit 8 which is the final visit of the study. A delay of  $\pm 5$  days is acceptable.

#### Final Visit 8 (Close-out visit)

- Ataxia rating scales (SARA, SCAFI)
- Documentation of frequency of physiotherapy and speech therapy (hours per week)
- Self-administered questionnaires (EQ-5D-5L, BDI-II, FSS)
- Documentation of adverse events
- Documentation of concomitant medication

### 10.2.6 Premature termination of trial / drop-out visit

The following procedures will be performed for subjects who withdraw from the trial and will terminate the trial prematurely. The premature termination visit ("drop-out visit") is scheduled 4 weeks after taking the last dose of study medication.

If a patient prematurely terminates treatment period 1, an immediate start of treatment period 2 after a wash-out period of 4 weeks is possible. In this case no premature termination visit should be conducted. The trial will be continued with treatment period 2 at visit 5.

If a patient prematurely terminates treatment period 2, the premature termination visit has to take place.

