| Trial Endpoints  | 
Primary efficacy endpoint:
 
SARA total score: absolute changes at the end of each treatment period compared to the period-level baseline defined as SARA score at visit 2 (treatment period 1) and at visit 5 (treatment period 2)
 
Key secondary endpoint(s):
 
SCAFI and subscores of SARA, QoL (EQ-5D-5L), depression (BDI-II), fatigue (FSS): absolute changes at the end of the 6-week treatment period compared to the period-level baseline defined as score at visit 2 (treatment period 1) and at visit 5 (treatment period 2).
 
Additionally, change scores at follow-up visit will be assessed.
 
Assessment of safety:
 
Documentation and reporting of side effects (AEs, SAEs, SUSARs)
 |

Confidential

|                           |                                                                                                                                                                                                                                                                                                                                                                                                                                                                                                                                                                                                                                                                                                                                                                                                                                                                                                                |

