### 6.2 Primary Efficacy Endpoint

The primary efficacy endpoint is defined as the absolute changes in SARA total score from period-level baseline to the end of the 6-weeks treatment period (verum/ placebo), i.e. the difference between post-treatment values and the corresponding period-level baseline values:

$$\text{Delta (SARA}_{\text{total}}) = \text{SARA}_{\text{total}} (\text{post-treatment}) - \text{SARA}_{\text{total}} (\text{period baseline})$$

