**Confidential**

- the intake of concomitant medications not permitted during the trial
- missed evaluations
- non-compliance with the IMP (e.g. intake of trial drug < 1.5 g daily during treatment period (week 3-6), depending on the duration of intake per treatment period and drug counting)
- any non-adherence to the protocol that would have an impact to the subject's rights, safety or welfare.

Minor protocol deviations may include, but are not limited to, e.g.:

- intake of trial drug < 5 g daily and > 1.5 g daily during the treatment period (week 3-6), depending on the duration of intake per treatment period
- unscheduled visits

After a subject has been enrolled, it is the investigator's responsibility to make a reasonable effort to correct any protocol violations and to continue the subject's participation in the trial. Protocol violations do not justify withdrawal of a subject from the trial.

Protocol violations will be reported to the sponsor/sponsor delegated person during the course of the trial in the monitoring reports.

Protocol violations will be listed and the impact on the evaluation of the subjects concerned will be discussed and evaluated at regular time intervals (depending on the amount of protocol violations), and prior to unblinding for a statistical analysis. Handling of major deviations in statistical analyses will be fixed during a blinded data review before unblinding.

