### 16.2 Termination of the Trial for Individual Subjects

If the clinical trial is prematurely terminated or suspended for any reason, the investigator should promptly inform the subjects and ensure appropriate therapy and follow-up.

Where required by the applicable regulatory requirements, the competent authority(ies) and the ethics committee(s) will also be informed.

There are different grades of deviations from the study flow ranging from minor, major protocol violations, (such as delayed or unscheduled study visits, discontinuation of taking the study drug, taking medication listed under prohibited therapy / concomitant medication (see protocol violations section 13.5) to complete withdrawal. Complete withdrawal should be a rare exception.

Whenever a subject is withdrawn totally from the trial, a complete final examination as scheduled for the premature termination/dropout visit should be conducted, and the circumstances of the withdrawal or discontinuation have to be recorded in detail in the medical file and the CRF.

If a subject does not return for a scheduled visit, every effort should be made to contact the subject (e.g. by *telephone visit* to assess and document treatment compliance, safety, or concomitant medication/ therapy) in order to avoid loss-to follow-up or dropout. These efforts have to be documented in the medical file.

Regardless of any decision to modify or discontinue their assigned intervention, study participants should be retained in the trial whenever possible to enable follow-up data collection and prevent missing data. In any circumstance, every effort should be made to document (key) subject outcomes, if possible. The subject has to be requested to return all unused investigational product(s), if applicable, and followed-up regarding any unresolved adverse events.

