### 16.2.1 Termination by the Subject

Subjects may withdraw totally from the study trial at any time at their own request without stating the reason(s) for withdrawal. Nevertheless the investigator should inquire about the reason for withdrawal. They will experience no disadvantage as a result of this decision and no alternative therapy will be withheld by the investigator.

In this case the investigator is urged to ask the subject to return for a premature termination / dropout visit and to document information as much as possible in the CRF as defined in premature termination / dropout visit (see section 10.2.6).

Treatment discontinuation in treatment period 1: patient can be enrolled into treatment period 2 after a 4 week wash-out period. This would be classified as a minor protocol violation.

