### 16.2.2 Termination by the Investigator

Subjects may also be withdrawn at any time at the discretion of the investigator for safety, behavioral, or administrative reasons, e.g.

- Occurrence of intolerable adverse events and which would constitute an unacceptable high risk for the subject
- Medically indicated e.g. because it is found that inclusion/ exclusion criteria were violated
- Continuation is unacceptable because risks outweigh the benefits
- Pregnancy
- Lack of compliance of the subject (e.g. taking prohibited medication)
- Significant protocol violations
- Logistical reasons (e.g. subject changes his/her doctor or hospital or moves to another location)

Whenever a subject is withdrawn from the trial, the reasons of the withdrawal or treatment discontinuation together with the date of last intake have to be recorded in detail in the patient's medical records and the CRF. If a patient drops out totally from the study and no data will be collected after withdrawal, a complete final examination (dropout visit, see 10.2.6) should be conducted. In particular, every effort should be taken to assess the primary outcome. The subject has to be requested to return all unused investigational product(s), if applicable, and followed-up regarding any unresolved adverse events.

If a subject does not return for a scheduled visit, every effort should be made to contact the patient in order to regain him for further visits according to the protocol.

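### Section 10.2.6 does not prescribe the week-6 SARA for patients who stop treatment early, in conflict with sections 16.2, 16.2.2 and 13.4

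*Protocol*

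**What the plan says.** Section 6.2 defines the primary endpoint as "absolute changes in SARA total score from period-level baseline to the end of the 6-weeks treatment period". The synopsis gives the "period-level baseline defined as SARA score at visit 2 (treatment period 1) and at visit 5 (treatment period 2"). Section 13.1 feeds the primary mixed model with the changes at the 2-week and 6-week visits.

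Section 10.2.6 handles early stopping in two ways:

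- **Stop in period 1, then continue.** Period 2 may start after a 4-week wash-out. "In this case no premature termination visit should be conducted. The trial will be continued with treatment period 2 at visit 5".
- **Withdrawal from the trial, or stop in period 2.** A drop-out visit with SARA is held. It "is scheduled 4 weeks after taking the last dose of study medication".

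Other sections pull the other way. Section 16.2 says that, whatever happens to treatment, "study participants should be retained in the trial whenever possible to enable follow-up data collection and prevent missing data". Section 16.2.2 says that "every effort should be taken to assess the primary outcome", but attaches this to the drop-out visit of 10.2.6. Section 13.4 commits to analysis as randomised, discontinuers included. Section 13.6 analyses those who stop treatment with whatever data exist and uses no imputation in the primary analysis.

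On classification, section 16.2.1 says of a patient who stops in period 1 and enters period 2: "This would be classified as a minor protocol violation". Section 13.5 gives as an example of a major violation "intake of trial drug < 1.5 g daily during treatment period (week 3-6"), with a qualifier about duration of intake.

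**The concern.** An intention-to-treat comparison at week 6 needs a week-6 score from patients who stopped treatment as well as from those who did not. Section 10.2.6 is where a site will look when a patient stops, and it does not ask for that score. In period 1 it moves from the stop directly to visit 5. For withdrawals and period-2 stops it asks for a rating at a time set by the last dose rather than by the start of the period.

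This is a rule about data collection, so a later analysis plan cannot repair it. A score that was never taken can only be modelled. If patients who stop differ from those who continue in how their ataxia would have developed, the primary observed-data analysis rests on an assumption that the trial will have collected little data to check.

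**Working it through.** **Inputs.** Period length 42 days, wash-out 28 days, and visit 4 at day 42 with a window of ±5 days (section 2). Drop-out visit 28 days after the last dose, and period 2 possible after a 28-day wash-out (10.2.6). Let s be the day within the period on which treatment stops.

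**Timing of the next SARA that 10.2.6 names.** This is day s + 28 at the earliest: visit 5 for a period-1 stopper who continues, the drop-out visit for the others. It falls in the week-6 window only if 37 ≤ s + 28 ≤ 47, that is, for s from 9 to 19. In period 1, visit 4 precedes visit 5 if s + 28 > 42, that is, s > 14.

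| Stop day s | Next named SARA (s + 28) | Within day 37–47? | Days off drug at nominal day 42 (42 − s) | Visit 4 before earliest visit 5? |
|---|---|---|---|---|
| 7 | 35 | no | 35 | no |
| 14 | 42 | yes | 28 | same day |
| 21 | 49 | no | 21 | yes |
| 28 | 56 | no | 14 | yes |
| 35 | 63 | no | 7 | yes |

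Two things follow. The named SARA is always 28 days off drug, and in period 1 it already serves as the period-2 baseline. For stops after about day 14, visit 4 can be held on schedule without touching period 2; 10.2.6 simply does not ask for it. Visit 3 (day 14) comes before s + 28 for every s, and 10.2.6 does not mention it either.

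**Does the sample size already cover this?** First the plan's own figure (section 13.3): paired t-test, difference 1.5, SD of the difference 4.2 as stated, two-sided 5%, power 90%. The noncentrality is (1.5 / 4.2) × √n. The exact calculation gives n = 85, hence 86 for two sequences, with 90.6% power at 86. Dropout: 86 / 0.8 = 107.5, so 108. Both figures reproduce. (How 4.2 relates to the stated correlation of 0.6 is a separate matter and does not affect this point.)

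With a complete pair for all 108 patients, power would be 95.7%. The protocol gives no rate of treatment stopping, so the shares below are assumptions:

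| Assumed share of 108 without a pair | Pairs left | Power |
|---|---|---|
| 5% | 103 | 94.8% |
| 10% | 97 | 93.6% |
| 20% | 86 | 90.6% |

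Power holds across this range. The 20% allowance (108 − 86 = 22 patients, 22 / 108 = 20.4%) concerns failure to complete both phases, not treatment stopping, and it does nothing about bias.

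**Violation classes.** A patient who stops by day 14 takes nothing in weeks 3 to 6. Section 16.2.1 makes this minor if the patient enters period 2, while the same intake fits the major example in 13.5. Section 13.4 separately allows per-protocol exclusion for insufficient treatment.

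**The case against.** The strongest reply is that 10.2.6 deletes nothing. It withholds the termination visit only. It does not cancel visit 4 or visit 7, which the schedule fixes six weeks after the period starts, and moving on to period 2 is an option. Section 16.2 governs patients who stop treatment and asks for their outcomes, so for stops after about day 14 a site can satisfy both sections. This stands. A reader might infer that the primary outcome is lost by rule, but the documents show an omission and a conflict, not a prohibition.

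Second, no section says that the drop-out SARA enters the model as a week-6 value. Section 13.1 names only the 2-week and 6-week visits. This also stands: an off-drug rating passed off as post-treatment is a possibility to close off, not something planned.

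Third, section 13.6 promises sensitivity analyses under informative missingness, and patients who reach visit 3 contribute to the mixed model. Both are true and both limit the harm. Neither supplies the missing week-6 score.

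Fourth, a week-6 rating in someone who has stopped is itself off drug, for 21 days after a stop on day 21, so it may seem inconsistent to want it and reject the drop-out rating. The two differ in purpose. The scheduled rating is the endpoint at its defined time, whatever the exposure, which is what section 13.4 asks for. The drop-out rating is taken at a time that depends on the stop, and visit 5 would have to be both the outcome of one period and the baseline of the next. For stops up to about day 14 the scheduled date no longer precedes the earliest visit 5, so a SARA at stopping is needed there.

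Finally, the violation list in 13.5 is illustrative, and its handling is settled at the blinded data review. The clash with 16.2.1 is one of labels.

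**Conclusion.** The point holds as a gap in data collection and a conflict between sections. Section 10.2.6 prescribes no end-of-period SARA for period-1 stoppers who continue, and only a rating 28 days off drug for withdrawals and period-2 stoppers. Sections 16.2, 16.2.2 and 13.4 require more than that. It should be corrected, because week-6 values not taken cannot be recovered by the observed-data primary analysis.

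Its size cannot be stated. The number affected lies somewhere within or beyond the 22 planned non-completers, since a patient can stop treatment and still attend visits. A reader might infer that those affected stop because of intolerance or lack of effect, and might put a percentage on the resulting overstatement. The documents support neither. The rule covers any early stop, section 5 describes good tolerability, and such a percentage would need an invented stopping rate and an assumption of no benefit in stoppers, and would have to ignore both the visit-3 data and stops on placebo.

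The timing results rest on period 2 starting as early as 10.2.6 allows. If it starts later, there is more room for visit 4.

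**What to change.** Amend 10.2.6 to state that:

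- a patient who stops the trial drug but stays in the trial keeps the scheduled visit 4 or visit 7 SARA at nominal week 6 wherever it falls before the next period starts; the same sentence can cover visit 3 or 6 if not yet held;
- where it would not (period-1 stops up to about day 14), and for anyone leaving the trial, a SARA is taken at the time of stopping or leaving;
- scheduled week-6 values enter the intention-to-treat analysis whatever the treatment status, and SARAs taken at stopping are labelled by their actual time;
- neither the drop-out SARA four weeks off drug nor the visit-5 baseline is used as the week-6 post-treatment value.

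Align 16.2 and 16.2.2 with this text, and reconcile the minor label in 16.2.1 with the major example in 13.5. When period 2 may start, and which violation label applies, are for the sponsor to decide.

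The cost is amendment wording and a few extra SARA ratings. Visits 4 and 7 are already in the schedule, and the sample size does not change.
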